## STATEMENT OF COMPLIANCE

The trial will be conducted in accordance with International Conference on Harmonization Good Clinical Practice (ICH GCP), applicable United States (US) Code of Federal Regulations (CFR), and the BioMarin Terms and Conditions of Award. The Principal Investigator will assure that no intentional deviation from, or significant changes to the protocol will take place without prior agreement from the funding agency and documented approval from the Institutional Review Board (IRB), except where necessary to eliminate an immediate hazard(s) to the trial participants. All personnel involved in the conduct of this study have completed Human Subjects Protection and ICH GCP Training.

The protocol, informed consent form(s), recruitment materials, and all participant materials will be submitted to the IRB for review and approval. Approval of both the protocol and the consent form must be obtained before any participant is enrolled. Any amendment to the protocol will require review and approval by the IRB before the changes are implemented to the study. All changes to the consent form will be IRB approved; a determination will be made regarding whether a new consent needs to be obtained from participants who provided consent, using a previously approved consent form.

## 1 PROTOCOL SUMMARY

### 1.1 SYNOPSIS

**Title:** Vosoritide for Selected Genetic Causes of Short Stature

**Study Description:** Short stature can be caused by a number of different genetic defects, many of which directly affect the growth plates. Vosoritide, a C-type natriuretic peptide (CNP) analog, targets chondrocytes within the growth plate leading to increased cell proliferation and hypertrophy. We hypothesize that patients with selected genetic causes of short stature will respond to vosoritide treatment leading to increased growth velocity. This study will enroll patients with selected genetic causes of short stature for whom evidence exists to support the potential for improved growth. The subjects will be followed for a 6 month observation period to obtain baseline growth velocity, safety profiles and quality of life assessments. Subjects will then be treated with vosoritide for 12 months and will be assessed for safety monitoring and improvement in height outcomes. Subjects with a positive response to therapy will be given the option to continue in the extension phase of the study during which they will continue to receive vosoritide until growth cessation.

**Objectives:**

The primary objectives of the study are as follows:

- To evaluate the safety and tolerability of daily subcutaneous (SC) injections of vosoritide administered for 12 months in patients with selected genetic causes of short stature
- To evaluate the change from baseline in age-sex standardized annualized growth velocity after 12 months of daily SC injections of vosoritide in patients with selected genetic causes of short stature

- To evaluate the change from baseline in age-sex standardized height standard deviation score (SDS) after 12 months of daily SC injections of vosoritide in patients with selected genetic causes of short stature

The secondary objectives of the study are as follows:

- To evaluate changes in body proportions from baseline after 12 months of daily SC injections of vosoritide
- To evaluate changes from baseline in bone age/chronological age after 12 months of daily SC injections of vosoritide

The exploratory objectives of the study are as follows:

- To evaluate the pharmacokinetic (PK) profile of vosoritide in patients with selected genetic causes of short stature
- To evaluate changes from baseline in bone mineral density (BMD) after 12 months of daily SC injections of vosoritide
- To evaluate changes from baseline in vosoritide activity biomarkers and bone/collagen biomarkers after 12 months of daily SC injections of vosoritide
- To evaluate immunogenicity and assess impact on safety and efficacy measures after 12 months of daily SC injections of vosoritide
- To explore the relationship between genetic etiology and safety and efficacy
- To evaluate changes from baseline in quality of life using the QoLISSY scale after 12 months of daily SC injections of vosoritide

During the extension study, all of the primary, secondary and exploratory aims will remain the same, but the timeframe will be extended from 12 months until growth cessation or subject withdrawal from the study.

#### **Endpoints:**

The primary study endpoints include:

- Incidence of adverse events per subject with particular attention to Grade 3 and 4 adverse events as well as to rates of hypotension
- Change from baseline in age-sex standardized annualized growth velocity after 12 months of treatment
- Change from baseline in age-sex standardized height SDS after 12 months of treatment

The secondary study endpoints include:

- Change from baseline in seated height ratio after 12 months of treatment
- Change from baseline in arm span minus standing height after 12 months of treatment
- Change from baseline in bone age/chronological age after 12 months of treatment

During the extension study, all of the endpoints will remain the same, but the timeframe will be extended from 12 months until growth cessation or subject withdrawal from the study.

**Study Population:**

The study will include up to 75 pre-pubertal children ages  $\geq 3$  years 0 days AND  $\leq 10$  years 364 days for males,  $\leq 9$  years 364 days for females with selected genetic causes of short stature (as defined below). Children will be recruited throughout the United States and will be brought to Children's National Hospital for all study visits.

**Accrual Ceiling:**

We estimate screening up to 100 subjects to achieve the feasible sample size for the trial.

**Phase:**

I/II

**Description of**

**Sites/Facilities Enrolling**

**Participants:**

**Description of Study**

**Intervention:**

This is a single center study at Children's National Hospital. Recruitment will occur throughout the United States, and patients will be brought to Children's National Hospital for all study visits.

This is a pediatric, Phase I/II, open-label single dose study of up to 75 subjects with selected genetic causes of short stature. Subjects who are 3 to 10 years old inclusive for males and 9 years old inclusive for females who have genetic defects in one of the categories defined in the inclusion criteria and meet all eligibility requirements will participate. After enrollment, subjects will be followed for a 6 month observation only period to establish a baseline height velocity as well as safety profile and quality of life assessment. Vosoritide will then be administered daily via subcutaneous injection at a dose of 15  $\mu\text{g}/\text{kg}/\text{day}$  for 12 months. Subjects with a positive response (as defined in the inclusion criteria for extension phase) to therapy will be given the option to continue in the extension phase of the study during which they will continue to receive vosoritide until growth cessation or subject withdrawal from the study.

PK sampling as well as safety monitoring will be conducted for all subjects on the first day that the study drug is received. The safety monitoring includes a minimum of 8 hours post-dose observation on the first day of dosing. Vital signs will be monitored frequently on that day, including approximately every 10-20 minutes for the first 2 hours post dose. Additional assessments include anthropometric measurements, physical examination, laboratory monitoring, ECG, DXA scan, bone age and spine X-rays. On day 2, the subject will return to the clinical research center for their second injection as well as 2 hours of post-injection monitoring. On days 3-5, subjects will receive a daily telephone call to review symptoms and issues with medication administration. After day 5, phone calls will occur on a bi-weekly schedule in-between study visits for months 1-5. During all telephone calls, adverse events as well as medication administration compliance will be assessed.

Subjects will return to Children's National Hospital for visits at 6 and 12 months. At those visits, anthropometric and safety assessments will be obtained as well as additional PK data at the 6 and 12 month visit.

Additional assessments noted in the prior paragraph will be repeated at the 6 and 12 month visits as detailed in the protocol. The dose of medication will be adjusted for weight at the 6 month visit if the subject has experienced weight changes.

During the extension phase, subjects will continue to be seen at Children's National every 6 months until growth cessation or subject withdrawal. Telephone visits will occur at the 3-month time point mid-way between each study visit.

**Study Duration:** 36 months; Extension phase of study may last up to an additional 15 years  
**Participant Duration:** 18 months; Extension phase may last up to ~15 years if a subject starts at age 3 years and stops growing at age 18 years

## 1.2 SCHEMA

### Vosoritide for Selected Genetic Causes of Short Stature Study Design

[figure not shown]

#### -6 Months Screening and Initiation of Observation Period

- Total n=up to 100
- Obtain informed consent
- Screen potential participants by inclusion and exclusion criteria
- Obtain history
- Obtain baseline physical exam and anthropometric measurements
- Obtain baseline screening labs, quality of life survey, and diagnostic studies
- Details provided in **Section 1.3, Schedule of Activities**

#### Months -5 through -1 Monthly phone calls

- Review health events
- Assess for adverse events/concomitant medications

#### Visit Day 1 (6months post screening) Vosoritide Initiation

- Intervention Group (n= up to 75)
- Initiate vosoritide treatment
- PK sampling
- Repeat laboratory, quality of life survey and diagnostic imaging evaluations, see **Section 1.3, Schedule of Activities**

#### Visit Day 2 Vosoritide Administration and Observation for Adverse Events

- Caregiver demonstrates proper medication administration in the clinic
- Assess for adverse events

#### Days 3 through 5 Daily Phone Calls

- Review medication administrations
- Review health events
- Assess for adverse events/concomitant medications

#### Months 1 through 5 Bi-weekly Phone Calls

- Review medication administrations
- Review health events
- Assess for adverse events/concomitant medications

#### 6 Month Visit Follow-up assessments of study endpoints and safety

- Obtain repeat quality of life survey, physical exam and anthropometric measurements
- Obtain repeat screening labs, PK sampling and diagnostic studies, see **Section 1.3, Schedule of Activities**

#### Months 7 through 11 Monthly Phone Calls

- Review medication administrations
- Review health events
- Assess for adverse events/concomitant medications

#### 12 Month Visit Follow-up assessments of study endpoints and safety

- Obtain repeat quality of life survey, physical exam and anthropometric measurements
- Obtain repeat screening labs, PK sampling, and diagnostic studies, see **Section 1.3, Schedule of Activities**

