## **EXTENSION PHASE DESIGN**

The extension phase will begin immediately after the 12-month visit. Eligible subjects will sign an addendum to the informed consent which outlines the details of participation in the extension study. Subjects will be seen in-person at Children's National every 6 months (+/- 2 weeks). Activities at the in-person study visits will include:

- Anthropometric Measurements
- Physical Exam
- Tanner Staging
- Vital Signs
- Quality of Life Survey
- Screening Labs
- Collagen X Marker sampling
- Vosoritide dose adjustment
- Review health events, concomitant medications, and medication administration
- Bone age X-ray – every 12 months
- DXA scan – every 24 months
- Additional safety imaging as needed due to clinical concern or prior abnormality

Additionally, subjects will have a telephone visit at the 3-month time point (+/- 2 weeks) between in-person visits. Activities at the telephone study visits will include:

- Review medication administration
- Review health events
- Assess for adverse events/concomitant medications

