### 1.3 SCHEDULE OF ACTIVITIES (SOA)

| Procedure                                                      | Screening and Initiation of Observation (-6 months) | Monthly Phone calls +/- 4 days (Months -5 through -1) | Day 1 visit (6 months +/- 2 weeks after screening) | Day 2 Visit | Days 3 through 5 Followed by Bi-weekly Phone calls +/- 4 days (Months 1 through 5) | 6 month visit (+/- 2 weeks) | Monthly Phone calls +/- 4 days (Months 7 through 11) | 12 month visit (+/- 2 weeks) | Early termination |
|----------------------------------------------------------------|-----------------------------------------------------|-------------------------------------------------------|----------------------------------------------------|-------------|------------------------------------------------------------------------------------|-----------------------------|------------------------------------------------------|------------------------------|-------------------|
| Informed consent                                               | X                                                   |                                                       |                                                    |             |                                                                                    |                             |                                                      |                              |                   |
| Medical History                                                | X                                                   |                                                       | X                                                  |             |                                                                                    |                             |                                                      |                              |                   |
| Parental anthropometrics a                          | X                                                   |                                                       |                                                    |             |                                                                                    |                             |                                                      |                              |                   |

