| PD markers g                                        | X                                                   |                                                       | X                                                  |             |                                                                                    | X                           |                                                      | X                            | X                 |
| DXA scan h                                          |                                                     |                                                       | X                                                  | *           |                                                                                    |                             |                                                      | X                            | X                 |
| Bone Age X-ray                                                 |                                                     |                                                       | X                                                  |             |                                                                                    |                             |                                                      | X                            | X                 |
| Spine X-ray i                                       |                                                     |                                                       | X                                                  | *           |                                                                                    | *                           |                                                      | X                            | X                 |

|                                  |   |   |   |   |   |   |   |   |   |
|----------------------------------|---|---|---|---|---|---|---|---|---|
| QoLISSY questionnaires           | X |   | X |   |   | X |   | X | X |
| Health events reviews            |   | X | X | X | X | X | X | X | X |
| Concomitant medications          | X | X | X | X | X | X | X | X | X |
| Study drug administration review |   |   | X | X | X | X | X | X | X |
| Adverse event reviews            | X | X | X | X | X | X | X | X | X |

a Both parents heights should be measured if available.

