#### 6.1.2 DOSING AND ADMINISTRATION

During the study, vosoritide will be administered as a single 15  $\mu\text{g}/\text{kg}$  subcutaneous injection given daily at approximately the same time each day whenever possible. The time of day of administration will be up to the individual subject and their guardian. It will be given 7 days per

week. The same injection site should not be used 2 days in a row, and sites should be rotated. Doses may be administered in any of the common subcutaneous areas (upper arm, thigh, abdomen, buttocks). If a dose is missed and noticed within 12 hours of the missed dose, it should be given at that time. If it has been more than 12 hours since the time of the missed dose, that dose should be skipped and the regular dose should be given the following day.

Vosoritide will be given for an initial 12-month period followed by an extension phase until cessation of growth or subject withdrawal from the study or until vosoritide becomes commercially available for the subject's indication. Doses will be given in the clinic during the Day 1, Day 2, 6 Month and 12 Month Visits prior to pharmacokinetic sampling. At the 6 month visit, the subject will be weighed. The dose of medication will be recalculated using the same 15 µg/kg dose but adjusted for the new weight. There will be no other dose increases in the protocol. After consultation with the DSMB, the dose may be reduced by 20% if the subject meets the individual stopping criteria on one occasion as detailed in **Section 7.1** below.

Subjects with a good response at 12 months will be offered participation in the extension phase of the study. A good response is defined in the inclusion criteria above. Subjects in the extension phase will continue to be seen in-person every 6 months at Children's National with telephone visits at the 3-month time point mid-way between in-person visits.

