### **Adverse Events**

The occurrence of AEs will be assessed continuously from the time the subject signs the ICF. The determination, evaluation and reporting of AEs will be performed as outlined in Section 8.3. Assessments of AEs will occur at the time points shown in the Schedule of Activities (Section 1.3).

NOTE: These safety assessments (except for X-rays) may be done at additional time points at the discretion of the PI in order to monitor for the development of adverse events or to ensure that the subject's baseline status has not changed which would preclude participation. X-rays are excluded as they increase the radiation exposure. For example, extra echocardiograms may be ordered if recommended by the study cardiologist.

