#### 8.3.4 TIME PERIOD AND FREQUENCY FOR EVENT ASSESSMENT AND FOLLOW-UP

The occurrence of an adverse event (AE) or serious adverse event (SAE) may come to the attention of study personnel during study visits or phone contacts with a study participant. Assessments for AE will occur as outlined in the Schedule of Activities (**Section 1.3**).

All AEs including local and systemic reactions not meeting the criteria for SAEs will be captured on the appropriate case report form (CRF). Information to be collected includes event description, time of onset, clinician's assessment of severity, relationship to study product (assessed only by those with the training and authority to make a diagnosis), and time of resolution/stabilization of the event. All AEs occurring while on study must be documented appropriately regardless of relationship. All AEs will be

followed until the event has resolved or any permanent sequelae are stable. The study team will work with the local clinicians to determine the characterization and severity of an AE and the proper course of treatment, if appropriate.

Any medical condition that is present at the time that the participant is screened will be considered as baseline and not reported as an AE. However, if the study participant's condition deteriorates at any time during the study, it will be recorded as an AE.

Changes in the severity of an AE will be documented to allow an assessment of the duration of the event at each level of severity to be performed. AEs characterized as intermittent require documentation of onset and duration of each episode.

The study coordinator, with supervision of the PI, will record all reportable events with start dates occurring any time after informed consent is obtained until 7 (for non-serious AEs) or 30 days (for SAEs) after the last day of study participation. At each study visit, the investigator will inquire about the occurrence of AE/SAEs since the last visit. Events will be followed for outcome information until resolution or stabilization. For events that are not resolved or stable at the last study visit, the study team will continue to contact the family by phone on a weekly basis until resolution or stabilization.

---

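### Section 8.3.4 requires new events to be recorded for 7 or 30 days after participation ends, but neither schedule of activities has a contact in that window

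*Protocol*

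**What the plan says.** **Recording rule.** Section 8.3.4 has the coordinator record reportable events that start at any time from consent "until 7 (for non-serious AEs) or 30 days (for SAEs) after the last day of study participation".

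**When events are asked about.** Section 8.2 (Adverse Events) states: "Assessments of AEs will occur at the time points shown in the Schedule of Activities (Section 1.3". Section 8.3.5 places formal review at each scheduled visit and call, and asks families to tell the team promptly about any event.

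**Where the schedules end.** The main-study schema in Section 1.2 stops at "12 Month Visit Follow-up assessments of study endpoints and safety". In the main table of Section 1.3 the closing columns are "12 month visit (+/- 2 weeks) | Early termination". The row "Adverse event reviews" is marked at both, and there is no later column. The extension table repeats yearly and also closes with Early Termination. Between extension visits, "subjects will have a telephone visit at the 3-month time point (+/- 2 weeks) between in-person visits".

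**Dosing at the last main-study visit.** Section 6.1.2: "Doses will be given in the clinic during the Day 1, Day 2, 6 Month and 12 Month Visits prior to pharmacokinetic sampling".

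**Contact after the last visit.** Section 8.3.4 provides weekly calls, but only for events that have not resolved or stabilised by that visit.

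**The concern.** The protocol defines a collection window and provides no scheduled means of collecting in it. For a child who leaves at Month 12, the window opens on a day when a dose was given. Anything new that starts after the family goes home reaches the database only through an unprompted report.

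Incidence of adverse events per subject is a primary endpoint (Section 3), and every child who receives a dose is in the safety analysis (Sections 9.3 and 9.4.4). Events that nobody asks about cannot be recovered at the analysis stage, whatever the SAP says. The final listing would also look complete to day 7 or day 30 when that stretch had only been passively observed.

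**Working it through.** The protocol states no figure for this point, so there is none to reproduce. The check compares the texts and adds calendar arithmetic.

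**Inputs**
- Recording window after the last day of participation: 7 days (non-serious AEs) and 30 days (SAEs), from 8.3.4.
- Last scheduled contact in the main study: 12 Month Visit (+/- 2 weeks) or Early Termination, from 1.3.
- Participation without the extension: 18 months (synopsis), made up of 6 months of observation and 12 of treatment. The 12 Month Visit is therefore the last day.
- Latest scheduled sample after the Month 12 dose: urinary cGMP at 4 hours, footnote g of the main table in 1.3.
- First contact for a child who continues: telephone visit at 3 months +/- 2 weeks, from the extension table.
- Assumption: 12 months of treatment is 365 days, with the last dose and last visit on the same day (6.1.2 supports the latter for the 12 Month Visit).

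**Step 1. Scheduled contacts in the window**
- Child ending at Month 12: 0 in days 1 to 7 and 0 in days 1 to 30.
- Child ending at Early Termination: 0 and 0.
- Child ending in the extension: 0 and 0.

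**Step 2. Unsolicited share of recording time for a child ending at Month 12**

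Share = window / (treatment days + window).
- SAEs: 30 / (365 + 30) = 30/395 = 0.076, about 8%.
- Non-serious AEs: 7 / (365 + 7) = 7/372 = 0.019, about 2%.

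Moving the visit to the edges of its window changes little. At 351 and 379 days the SAE share is 30/381 = 7.9% and 30/409 = 7.3%. The non-serious share is 7/358 = 2.0% and 7/386 = 1.8%.

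**Step 3. The same calendar days in a child who continues**

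The first contact falls at about 91 +/- 14 days, that is, day 77 to day 105 after the 12 Month Visit. The first 30 days are then asked about by recall, 77 - 30 = 47 to 105 - 30 = 75 days after day 30. For this child those days are on-treatment study time. The 7- and 30-day window has not opened, and when it does open Step 1 applies.

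**The case against.** **A recording duty with passive reporting is not a contradiction.** Section 8.2 says events are assessed continuously from consent, 8.3.4 obliges the coordinator to record through day 7 or 30, and 8.3.5 encourages families to report. Neither 8.2 nor 8.3.4 confines assessment to the schedule. This stands: the two texts can both be obeyed. But the only active enquiry the protocol describes is at scheduled visits and calls, and the weekly calls do not look for new events.

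**Children who stop the drug are mostly still followed.** Section 7.1 keeps them in the study with their remaining procedures, so they have scheduled event reviews after their last dose. This stands. The gap affects children who leave the study itself, which 7.2 allows for an intolerable event and requires after a second period of non-compliance.

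**The link to the primary endpoint is not spelled out.** The protocol does not say whether events after participation count in the endpoint or in the risk comparison of 9.1, and the SAP may settle that. This stands as a limit on the consequence. It does not remove the collection gap.

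**A stronger reading is tempting.** A reader might infer that late events are sought only in children who respond and continue, so that ascertainment differs by outcome. The documents do not support this. The window runs from the last day of participation, which for a continuing child has not arrived at Month 12. When it arrives, it is just as unsolicited. Continuation is also not purely by response: growth-hormone-experienced children may continue below the 3 cm/year threshold, and consent and bone age also apply.

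**Larger shares can be computed but do not generalise.** For a stop at Month 6 (182 days) the SAE share would be 30/212 = 14%, and at week 4 it would be 30/58 = 52%. Both apply only to a child who leaves the study on the day of the last dose. No dose is documented for the Early Termination visit.

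**Conclusion.** The point holds as a mismatch between the recording rule and both schedules. New events in the 7- and 30-day windows are solicited in no child, whichever way participation ends. The likely effect is some under-capture of late events relevant to a primary safety endpoint. The documents give no ground for calling it a differential bias by growth response.

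The size that can be stated is time, not events: about 8% of SAE recording time and about 2% of non-serious AE recording time from first dose, for a child ending at Month 12. This assumes 365 treatment days and that the 12 Month Visit is both the last dose and the last day of participation. With no event rates in the protocol, the number of missed events cannot be estimated. It may be small. The point is worth acting on because the remedy is cheap and makes the protocol's own window workable.

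**What to change.** Add one telephone call on or shortly after day 30 following the last visit, covering AEs, SAEs and concomitant medications. It should apply to every child ending participation: at the 12 Month Visit without entry to the extension, at Early Termination in either phase, and at the end of the extension. Show it as a column in both schedules in Section 1.3, and state in 8.3.4 that this call closes the 7-day and 30-day windows. A single call at day 30 suffices, because events with onset in the first 7 days can be asked about at the same time.

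The cost is one call per child, by staff who already make such calls, plus the two schedule columns and one sentence.
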